### Participant-Selection and Consent Process

Participants are identified during the oncologist assessment process at admission to the Oncology Department. If they agree, they will be forwarded to a space reserved for signing the free and informed consent form, an interview, and initial evaluation with the study researchers.

### Randomization, allocation concealment and Interventions blinding

Patients who meet the inclusion criteria are randomly assigned to the intervention or control group. Prior to randomization (http://www.randomizer.org), the attending oncologist review the absolute and relative contraindications to participating in the exercise program and will provide general information about the study. The allocation mechanism is carried out until 240 total patients are assigned. The assignment keys will be kept in a confidential file in the HUN and will be opened at the end of the study's analyses. To ensure masking, an alpha-numerical code will be assigned to each study group. This code is delivered to the associated researcher and is not revealed to the investigators in charge of processing the data until the analysis of the coded interventions is completed. Assessors of outcomes are blinded to patient data, including allocation at baseline and follow-up. Blinding is used for all laboratory analyses. Owing to the nature of the study, patients cannot be blinded to the exercise training modality. The study flow diagram is shown in Fig. 1.

**Figure 1 fig1:**
[figure not shown]
Flow diagram of the Study Protocol

All interventions take place at the Oncology Department of HUN (Pamplona, Spain) site facilities. Standard medical care are provided to all participants in all groups. Participants are randomly assigned to the following groups:•Usual care group (control): Participants randomly assigned to the usual care group receive normal hospital care, including physical rehabilitation when needed.•Multicomponent exercise group (intervention): The intervention consists of a multicomponent exercise training program which include supervised progressive resistance exercise training, balance-training and walking for 4 consecutive days. During the training period, patients are trained in 20-minute sessions twice a day (morning and evening).

The supervised multicomponent exercise training program include upper and lower body strengthening exercises, tailored to the individual's muscle function, using weight machines and aiming for 2–3 sets of 8–10 repetitions at an intensity of 40–70 % of 1 repetition maximum (RM) (Matrix, Johnson Health Tech, Ibérica, S.L., Madrid, Spain) combined with balance and gait retraining exercises that will progress in difficulty and functional exercises, such as rises from a chair. The second part of the session consists of functional exercises such as knee extension and flexion, hip abduction, balance movements, and daily walking in the hospital. The resistance exercises are focused on the major upper and lower limb muscles. Each resistance training session includes two exercises for the leg extensor muscles (bilateral leg extension and bilateral knee extension muscles) and one exercise for the upper limbs (seated bench press). In each session, subjects perform a specific warm-up with one set of very light loads for the upper and lower body. The training protocol is shown in Figure 2. Participants and their family members are carefully familiarized with the training procedures in advance. During hospitalization, two evaluations are carried out; the first one taking place on the day of inclusion in the study and the second one on the 6th day after said inclusion.

**Figure 2 fig2:**
[figure not shown]
Intervention group exercise protocol

One-Repetition Maximum (1RM).

### Outcome Assessment

The primary outcome is the change in functional status during the study period.•The functional capacity of participants is evaluated by the Short Physical Performance Battery (SPPB) (22), with the total score ranging from 0 (worst) to 12 points (best). This test evaluates balance, gait and rising from a chair. The standing balance test consists of the evaluation of the ability to maintain the standing position for 10 seconds with three different feet-positions: parallel, semi-tandem and tandem. The walking speed test measures the time needed to progress for 4 linear meters at the patient's usual speed, assigning a different score according to speed. Finally, the chair sit-to-stand part assesses the ability to stand from a chair five consecutive times without using the arms. The SPPB test has been shown to be a valid instrument for screening frailty and predicting disability, institutionalization and mortality.

Secondary outcomes of the study will include:•Handgrip strength. Handgrip strength is a useful tool for the measurement of functional capacity and predictor of disability (23). Each study participant will be asked to squeeze the dynamometer (Takei 5401 Digital Dynamometer) two different times and the higher score will be used to reflect handgrip strength. The measurement will be performed while the participant is seated, with the dominant hand with the elbow straight and the shoulder abducted at 15° (24, 25).•Changes in functional capacity in activities of daily living (ADLs) as measured with the Barthel Index (Spanish version) scale, which ranges from 100 (functional independence) to 0 (severe functional dependence) (26). This is an international, validated tool and it is the most used to measure disability (27).•Karnofsky' Index: The Karnofsky Performance Status (KPS) is a widely used method to assess the functional status of a patient.•Gait ability will be assessed using the 6-meter gait velocity test (GVT). Starting and ending limits will be marked on the floor with tapelines for a total distance of 8 m. Participants will be instructed to walk at their self-selected usual pace for two attempts. The results of both trials will be averaged to obtain a single value. The first and last meters, considered the warm-up and the deceleration phases, respectively, will not be included in the calculations of the gait assessment.•Dual-task GVT (arithmetic GVT). During the arithmetic dual-task arithmetic test (arithmetic GVT), we will assess the gait velocity while participants are counting backwards aloud from 100 one at a time. The cognitive score will be measured by determining how many numbers were counted backward (dual-task with arithmetic performance) (28).•Changes in mood status: the 15-item Yesavage Geriatric Depression Scale (GDS-VE), the Spanish Version, contains ten affirmative and five negative items, its score being normal when it ranges from 0 to 5 and a score greater than 5 suggesting depression (29).•Changes in the Trail Making Test (TMT) part A will be evaluated to assess executive dysfunction. The TMT is one of the most popular neuropsychological tests and is included in most test batteries. TMT-A requires an individual to draw lines sequentially connecting 25 encircled numbers distributed on a sheet of paper (30).•Maximal dynamic strength will be assessed using the 1RM test in the bilateral leg press, knee extension and bench press exercises using exercise machines (Matrix, Johnson Health Tech, Ibérica, S.L., Madrid, Spain). In the first assessment, the subjects will warm up with specific movements for the exercise test. Each subject's maximal load will be determined in no more than five attempts, with a 3-minute recovery period between attempts. During all neuromuscular performance tests, strong verbal encouragement will be given to each subject to motivate them to perform each test action as optimally and rapidly as possible. Qualified fitness specialists will individually monitor and carefully supervise all training sessions and provide instruction and encouragement during all sessions.•Changes in the quality of life will be measured by the Spanish version (31) of the EuroQol–5 Dimension (EQ-5D) questionnaire (32). It is an instrument that measures 5 dimensions of health status: mobility, self-care, usual activities, pain/discomfort, and anxiety/depression. Each dimension is rated according to the following levels: a) no problems; b) some problems; c) extreme problems. Besides, it contains a visual analogy scale to quantify the self-perceived health status, ranging from 0 (worst health state imaginable) to 100 (best health state imaginable).•Number of days alive after admission to the hospital.•Use of health resources: new admissions to the hospital, admission to nursing homes, visits to the emergency department and visits to the general practitioner.•Visual analogue scales (VAS) typically ask a patient to mark a place on a scale that matches their level of pain (33);•Mini-nutritional assessment- short form (MNA-SF): evaluation of nutritional status (34).•Brief Fatigue Inventory: validated tools to measure fatigue in patients with cancer (35).

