**Methods:**

We present the research protocol for a randomized controlled trial that will analyze whether an intervention applied to older patients (≥ 65 years) who are hospitalized for acute medical conditions in an Oncology Department improves function. A total of 240 hospitalized older patients will be recruited in the Hospital Universitario de Navarra, Pamplona, Spain, and they will be randomized. The intervention consists of a multicomponent exercise training program that will take place for 4 consecutive days (2 sessions/day). The control group will receive usual hospital care, which will include physical rehabilitation when needed. The primary end point will be the change in functional capacity from baseline to hospital discharge, assessed with the Short Physical Performance Battery (SPPB). Secondary end points will be changes in cognitive and mood status, quality of life, fatigue, strength (dynamic and handgrip), pain, nutrition, length of stay, falls, readmission rate and mortality at 3 months after discharge.

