After randomization, the research team (physiotherapist, sport science specialist, oncologist, and geriatrician) perform the baseline measurement and follow-up visits of functional, pharmacological, comorbidity, and cognitive assessment, as well as mobility and strength evaluations (Table 2). The multidisciplinary research team has previous experience in functional geriatric assessment and in the prescription of exercise in frail older patients in different clinical settings (12, 21). Regarding oncogeriatric patients, our previous findings confirm that a multicomponent exercise program improves measures of physical/cognitive functioning and quality of life in older adults with lung cancer under adjuvant therapy or palliative treatment, and some systematic reviews identify the best options and challenges in these type of patients (43, 44, 45, 46).

**Table 2 Tab2:** Time of measurement of the different variables in each of the participants of the study

**Measurement**	**T1 Baseline**	**T2 After training or control period**	**T3 1-month post decharge**	**T4 3-months post decharge**
Categorical scale of pain	x	x	x	x
Handgrip strength	x	x	x	x
Barthel Index	x	x	x	x
Karnofsky's Index	x	x	x	x
Geriatric depression Scale of Yesavage (GDS)	x	x	x	x
Short Physical Performance Battery (SPPB)	x	x	x	x
Gait Velocity Test (GVT)	x	x	x	x
Dual-task (verbal and arithmetic GVT)	x	x	x	x
Maximal isometric force of handgrip	x	x	x	x
1RM (Leg press, Chest press and Knee extension)	x	x	x	x
Muscle power at 50 % 1RM in Leg press	x	x	x	x
Quality of Life (EQ-5D-5L)	x	x	x	x
EORTC QLQ-C30	x	x	x	x
Geriatric syndromes	x	x	x	x
Brief Fatigue Inventory	x	x	x	x
Trail Making Test part A (TMT-A)	x	x	x	x
Laboratory parameters	x	x		
Diseases considered grouped by ACG of Salisbury and CIE-10 codes	x			
Cumulative Illness Rating Scale for Geriatrics (CIRS-G)	x			
Falls	x	x	x	x
Mini Nutritional Assessment (MNA)	x	x		

1RM: 1 Repetition Maximum;

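### The dual-task cognitive score is a raw count over a fixed walking distance, so it is confounded with gait speed, which the intervention aims to raise

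*Protocol article*

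**What the plan says.** The gait test is defined first under Outcome Assessment in the protocol article: "Gait ability will be assessed using the 6-meter gait velocity test (GVT"). The course is fixed: "Starting and ending limits will be marked on the floor with tapelines for a total distance of 8 m", with the first and last metre left out of the calculation. The pace is free: "Participants will be instructed to walk at their self-selected usual pace for two attempts".

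The next item is the arithmetic dual-task version of that test, in which "we will assess the gait velocity while participants are counting backwards aloud from 100 one at a time". Its cognitive score follows: "The cognitive score will be measured by determining how many numbers were counted backward (dual-task with arithmetic performance"). The item gives no counting period and no division by walking time.

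Table 2 schedules the dual task, listed as "Dual-task (verbal and arithmetic GVT"), at all four time points. The Abstract lists cognition among the outcomes: "Secondary end points will be changes in cognitive and mood status". The intervention description includes resistance work "combined with balance and gait retraining exercises that will progress in difficulty", as well as walking. Under Statistical procedures, quantitative variables are analysed by a linear mixed model containing time, group and their interaction; walking time is not in the model.

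**The concern.** When distance is fixed and pace is free, a faster walker has less time in which to count. The score then reflects two things at once: how fast the patient counts and how long the walk lasts. In most settings that would only add noise. Here the exercise programme is meant to improve gait, and gait speed is both a secondary outcome and a component of the SPPB. Treatment can therefore shift walking time in one arm and not in the other, and randomisation does not protect against that, because the shift arises after allocation.

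At stake is the interpretation of one secondary cognitive outcome. A gait benefit could show up as a lower cognitive score, a cognitive benefit could be partly cancelled, and a patient who deteriorates and slows could appear to count better.

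**Working it through.** The article states no figure for this outcome, so there is none to reproduce. The check is algebraic.

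**Inputs from the article.** Distance D = 6 m timed within an 8 m course; self-selected pace; score = count of numbers. The course is stated for the single-task gait test. It carries over because the dual task is named as that same test.

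**Inputs assumed.** The article gives no counting rate r and no gait speed v. I take r = 1 number per second for illustration (range 0.8 to 1.5) and speeds between 0.5 and 0.8 m/s.

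**Formulas.**
- Walking time: T = D / v
- Count: C = r × T = r × D / v
- Relative change when speed goes from v0 to v1 at constant r: C1/C0 − 1 = v0/v1 − 1, that is, a fall of 1 − v0/v1
- Rise in counting rate needed to keep the count level: v1/v0 − 1

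The relative change contains neither r nor D, so the percentages are the same for any counting rate and for 6 m or 8 m.

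**Results (6 m, r = 1 per second).**

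| Speed, m/s | Count before | Count after | Change | Rate change to break even |
|---|---|---|---|---|
| 0.60 to 0.65 | 6/0.60 = 10.0 | 6/0.65 = 9.2 | −7.7% | +8.3% |
| 0.6 to 0.7 | 10.0 | 6/0.7 = 8.6 | −14.3% | +16.7% |
| 0.6 to 0.8 | 10.0 | 6/0.8 = 7.5 | −25.0% | +33.3% |
| 0.6 to 0.5 | 10.0 | 6/0.5 = 12.0 | +20.0% | −16.7% |

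For 0.6 to 0.7 m/s, the absolute loss runs from 1.14 numbers (r = 0.8, 6 m: 8.00 to 6.86) to 2.86 numbers (r = 1.5, 8 m: 20.00 to 17.14).

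**Effect on the group comparison.** Suppose counting rate does not change in either arm, the exercise arm goes from 0.6 to 0.7 m/s and the control arm stays at 0.6 m/s (6 m, r = 1). The group-by-time contrast is then (8.57 − 10) − (10 − 10) = −1.43 numbers, with no difference in cognition. If the control arm slows to 0.5 m/s, it is (8.57 − 10) − (12 − 10) = −3.43.

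**Same data, scored as a rate.** C / T = (r × D / v) / (D / v) = r. Gait speed cancels, and the change is 0 in every row of the table.

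**The case against.** The strongest reply is that the sentence says what is recorded and does not forbid dividing it by time later. It cites a method source that is not at hand and may use a rate, and a condensed article commonly leaves scoring detail to the full protocol or analysis plan. Part of this stands: a fuller document may already normalise the count. But the article is not silent. It names the quantity that measures cognition, and that quantity is a count.

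Other points on that side do stand, and they limit what can be concluded:

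- A reader might infer that every patient who walks faster automatically scores worse. That holds only at an unchanged counting rate; someone whose rate rises at least in proportion to speed does not score lower.
- A reader might infer that a gait benefit would be reported as cognitive harm. The article also assesses gait velocity in the same dual-task walk, so the two can be read together and a rate can be derived if both were recorded. The count could mislead; it need not.
- A reader might infer that the trial's conclusion on cognition rests on a scale pointing the wrong way. The Conclusions section does not tie its statement to this score, and the Trail Making Test part A is a cognitive measure that does not depend on walking.
- A reader might object that wrong numbers are counted as right ones. The article does not say so; how errors are marked is detail an article may leave out, and it is no part of this point.
- The 25% figure needs a 33% gain in speed after a four-day programme, for which the article offers no basis. The smaller cases in the table should be read beside it.

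**Conclusion.** The point holds for this one secondary outcome. As defined, the dual-task cognitive score is inversely proportional to gait speed at a given counting rate. The comparison between arms is therefore biased towards apparent cognitive loss in an arm whose gait improves, and towards apparent gain in an arm whose gait slows. The stated model does nothing to remove this.

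The direction follows from the article's own definitions, given that the dual task uses the gait test's fixed course. The size depends on speeds the article does not give: from 7.7% for a gain of 0.05 m/s to 25% for a gain of 0.2 m/s, both from an assumed 0.6 m/s. The bias is offset only if counting rate rises at least as much, proportionally, as gait speed. The SPPB primary outcome, the Trail Making Test part A and the sample size are not affected.

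**What to change.** Define the dual-task cognitive score as numbers counted per second of the same walk, that is, the count divided by the walking time over the segment in which the numbers are counted. State that the raw count will not be analysed as a cognitive score. Dual-task gait velocity is already assessed and needs no change.

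The cost is about one sentence in the outcome definition. The walk must already be timed to obtain velocity, and the numbers are already counted. For patients already assessed, the rate can be derived wherever count and time were both kept.

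The one small downside is that count and time must cover the same segment. If numbers were counted over the full 8 m but time was taken over the central 6 m, the rate at a steady pace would be too high by 8/6 − 1 = 33%. A change of practice between visits would then look like a change in the patient. The definition should name the segment.

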
### Statistical procedures

The sample size calculation was performed using the GPower v. 3.1 software, adopting a significance level of α = 5%, a correlation between pre-and post-intervention values of the Short Physical Performance Battery (SPPB) of ϱ = 0.5 and a standard deviation for the SPPB of σ = 2.5, the required sample size to have a power of 90% to detect a minimum difference of 1 point between groups in the post–pre SPPB score is 101 patients per group. Taking an expected loss of patients at follow-up of 15% into account, the final sample size required is 120 per group.

The description of the sample by the group will be conducted using statistics such as means and standard deviations or medians and interquartile ranges for the quantitative variables, and frequencies and percentages for the qualitative variables. For comparisons between groups at baseline, t-tests or Mann–Whitney U tests will be used for continuous variables, depending on normality, which will be checked for each using the Kolmogorov-Smirnov test and normal probability plots, and the chi-square test or Fisher's test will be used for categorical variables.

To determine the efficacy of the intervention in the quantitative variables, such as the SPPB, we will use linear mixed models, using time, group and time and group interaction as categorical covariates. In the case of qualitative or categorized variables (such as whether an improvement of a given magnitude between pre-and post-intervention has been achieved or not), comparisons between groups will be conducted with the chi-square test or Fisher's test, and complemented with logistic regression if additional adjustment is needed. Effect sizes between-group will be computed based on Cohen's d and the 95% confidence interval. The level of statistical significance will be 0.05. Data will be analyzed using an intention-to-treat approach with R and SPSS statistical packages.

In order to check the assumption that the potential impact of missing data is negligible (created by a missing complete at random or a missing not at-random mechanism), best–worst and wors`t-best case sensitivity analyses will be used. When the missing data surpasses 5% and if this is supported by the previous sensitivity analysis, a missing at-random mechanism will be assumed and missing values will be imputed using the R package MICE (Multivariate Imputation via Chained Equations). If the proportion of missing data is very large (rises over 40%) on important variables, trial results will be considered hypothesis-generating results.

We will compare the proportion or number of adverse events between groups, using chi-square test or Mann-Whitney U test.

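### The stated inputs and mixed model give about 81% power at 101 patients per group, not 90%; 101 matches a baseline-adjusted variance that the text does not specify

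*Protocol article*

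**What the plan says.** All planning inputs stand in the Statistical procedures section of the protocol article:

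- Level: "adopting a significance level of α = 5"%. Sidedness is not stated, but the same section pairs a 0.05 level with 95% confidence intervals.
- Correlation: "a correlation between pre-and post-intervention values of the Short Physical Performance Battery (SPPB) of ϱ = 0.5".
- Variability: "a standard deviation for the SPPB of σ = 2.5".
- Target: "the required sample size to have a power of 90% to detect a minimum difference of 1 point between groups", the difference being taken in the post-minus-pre SPPB score.
- Result: 101 per group, raised to 120 per group for 15% loss. The software is named (GPower), but the test family chosen in it is not.

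For the efficacy analysis of quantitative outcomes, including SPPB: "we will use linear mixed models, using time, group and time and group interaction as categorical covariates". Baseline SPPB is not named as a covariate, and no constraint on the baseline means is mentioned.

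Two other places bear on the point. The Discussion reports that, with a third of the planned patients recruited, power for a 1-point difference is nearly 50%. The text introducing Table 2, under Participants and eligibility, places the baseline assessment after randomization.

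**The concern.** The section names its contrast (difference in change), its inputs, its model and its answer, and the four do not agree. A correlation of 0.5 is exactly the value at which a change score gains nothing: subtracting baseline adds as much variance as it removes. The stated inputs should therefore give the sample size of an unadjusted comparison with SD 2.5, which is well above 101.

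Two things are at stake. The type II error for the primary outcome would be about 19%, when the plan says 10%, so a null result would be read against overstated power. And if the model is used as written, the trial forgoes a 25% reduction in variance that its own baseline SPPB data could supply.

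**Working it through.** **Inputs.** Difference 1 point; σ = 2.5; ρ = 0.5; 1:1 allocation; 101 per group; 15% loss (all from Statistical procedures). Two-sided 5% is an assumption, varied below. The SD is taken to be equal before and after.

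**Step 1: the contrast as written.**
SD of change = σ·√(2(1 − ρ)) = 2.5·√(2 × 0.5) = 2.5.
n per group = 2(1.960 + 1.282)² × 2.5² / 1² ≈ 131.3, so 132 by the normal formula and 133 with the noncentral t.
The stated 101 is not reproduced.
Power at 101: standard error = 2.5·√(2/101) = 0.352; 1/0.352 − 1.960 = 0.883; Φ(0.883) = 81.1%. The noncentral t gives 80.8%, and a simulation of 20,000 trials also gives 80.8%.

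**Step 2: the planned model.** Baseline is one of the outcome times, and group, time and group-by-time are all free. With complete data, the baseline-to-discharge interaction contrast is then the difference between arms in mean change, with per-patient variance 2σ²(1 − ρ) = 6.25. This is the quantity in Step 1.

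**Step 3: baseline-adjusted variance.**
Residual SD = σ·√(1 − ρ²) = 2.5·√0.75 = 2.165; variance 4.6875, which is 25% below 6.25.

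| Analysis (two-sided 5%, noncentral t) | SD | n/group for 90% | Power at 101 | at 102 | at 120 |
|---|---|---|---|---|---|
| Change score or free interaction | 2.5 | 133 | 80.8% | 81.1% | 87.0% |
| Adjusted for baseline SPPB | 2.165 | 100 | 90.4% | 90.7% | 94.6% |

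Here 102 is 120 × 0.85, and 120 is the case of no loss before the discharge assessment. Simulation of the adjusted analysis at 101 gives 90.3%.

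**Step 4: other routes to a figure near 101.**
- One-sided 5%, change score: 108 per group needed; 88.3% power at 101.
- Change score at 80% power: 99 to 100 per group.
- GPower's between-factors repeated-measures routine (f = 0.2, two measurements, ρ = 0.5): 200 in total, 100 per group. This tests the average of pre and post, not their difference.
- Change score with ρ of about 0.62 instead of 0.5: 100 per group.

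**Step 5: loss.** 101/0.85 = 118.8, so 120 is adequate for 101. For 133 it would be 133/0.85 = 156.5, so 157 per group.

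**Step 6: the Discussion's figure at one-third recruitment.** A third of 240 is 80, or 40 per group; less 15% that is 34.

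| Analysis (two-sided) | 34/group | 40/group |
|---|---|---|
| Change score | 37% | 42% |
| Baseline-adjusted | 47% | 53% |

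**The case against.** The strongest reply is that the planning was sound and only the model sentence is too short. The adjusted analysis needs 100 per group. If its standardised effect, 1/2.165 = 0.462, is rounded to 0.46, the answer is 101. The Discussion's nearly 50% also sits closer to the adjusted figures than to 37% or 42%. A condensed article may leave the treatment of baseline to an analysis plan that is not shown.

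Part of this stands. Baseline adjustment is a plausible origin of 101, and the fault may lie in the description. But the article does more than omit a detail. It names the change score as the target and lists the model terms, and those give 81%.

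A reader might go further and infer that 101 can only have come from baseline adjustment. The document does not support that. It names neither the test family nor the sidedness, and other routes also land near 100. Nor does the Discussion's figure settle it, since a one-sided change-score test at 34 per group has 49.5% power.

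It can also be said that planned power no longer matters, because the Abstract concedes that the recruitment target will not be met. That limits the practical effect of the 101, but it does not correct the figure. The same choice of analysis moves the power at present recruitment by about 10 points.

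Finally, the 15% loss concerns follow-up, while the primary endpoint is at discharge, so more than 102 per group might have been evaluable. True, but all 120 give 87%, still short of 90%.

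**Conclusion.** The point holds. Under the stated SD, correlation, contrast and model, power at 101 per group is about 81%, and it is 87% if all 120 per group are evaluable; 90% would need 133 evaluable per group. The stated 90% is consistent with a baseline-adjusted analysis that the text does not specify, but how 101 was obtained cannot be established.

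This rests on a two-sided 5% test, equal SDs at both times, complete data for the contrast, and reading the model sentence as having unconstrained baseline means. A one-sided test narrows the gap (88.3%) without closing it.

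It would be wrong to infer that the trial must recruit more, or that the mixed model is invalid. Nothing here affects type I error or introduces bias. The error is in the stated power and in its mismatch with the stated analysis.

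**What to change.** Choose one of two corrections in Statistical procedures:

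1. **Keep the written model** and restate the power of 101 per group as about 81%. This costs one sentence and depends on nothing else.
2. **Specify a baseline-adjusted primary analysis**: either ANCOVA of discharge SPPB on group and baseline SPPB, or the mixed model with a common baseline mean for both arms. State that the sample size rests on σ·√(1 − ρ²) = 2.165. This costs one model term and no new data, but it has two conditions. The sponsor must confirm that baseline SPPB was measured without influence of allocation, because the text introducing Table 2 places it after randomization. And since baseline results are already reported, the change needs a dated justification.

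With either option, state the sidedness and the GPower test family, and bring the Discussion's figure into line: 37% to 42% for the change score, or 47% to 53% with baseline adjustment, at 34 to 40 per group. Neither option requires extra patients.

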The recruitment of this type of patient is a major challenge given the obvious differences compared to patients traditionally recruited in geriatric departments, with additional aspects beyond the purely medical issues, such as psychological aspects, the appropriate time to start complementary treatments or the interaction with baseline treatments such as chemotherapy when prioritizing the optimization of pharmacological and non-pharmacological therapies. All these factors will provide evidence that will help to update clinical guidelines related to this type of intervention in the future. At the present time, given recruitment of one-third of the initial estimate, we would have a power of almost 50% to detect as statistically significant a difference of 1 SPPB between groups.

If our hypothesis is correct, it opens the way to the modification of the hospitalization system and the current oncogeriatric management of patients with medical conditions. If we modify the current guidelines, it is likely that older adults after admission will present lower levels of functional and cognitive deterioration, predictably a better quality of life and lower consumption of health resources (lower readmissions, less institutionalization, among others).

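### The stated SPPB model does not condition on baseline, so it loses precision and leaves half of any chance baseline imbalance in the primary contrast; the planned baseline tests do not help

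*Protocol article*

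**What the plan says.** All of the analysis wording is in the protocol article, Statistical procedures.

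- **Efficacy model.** For quantitative outcomes such as the SPPB: "we will use linear mixed models, using time, group and time and group interaction as categorical covariates". No baseline covariate and no common-baseline constraint is listed. The Abstract defines the primary endpoint as the SPPB change from baseline to discharge.
- **Baseline comparison.** After descriptive summaries by group, the section adds: "For comparisons between groups at baseline, t-tests or Mann–Whitney U tests will be used for continuous variables". The choice between the two depends on normality, checked with a Kolmogorov-Smirnov test and probability plots. Likewise "the chi-square test or Fisher's test will be used for categorical variables". No later step is tied to these results.
- **Sample size.** The calculation uses a pre-post correlation of 0.5 and "a standard deviation for the SPPB of σ = 2.5". It gives "the required sample size to have a power of 90% to detect a minimum difference of 1 point between groups" as 101 per group, raised to 120 for 15% loss. The significance level is 0.05.
- **Recruitment.** The Abstract says that the target will not be met. The Discussion adds: "given recruitment of one-third of the initial estimate, we would have a power of almost 50" per cent for a 1-point difference.

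**The concern.** With free group, time and group-by-time terms, the discharge contrast is each arm's mean SPPB change, differenced. That takes off the whole baseline difference. With a pre-post correlation of 0.5, only half of a chance baseline difference is expected to persist to discharge, so subtracting all of it over-corrects. The arm that happened to start higher looks worse on change, and the arm that started lower looks better.

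Two things are at stake. One is power, in a trial that is already far short of its target. The other is how far the estimate from the one randomisation actually carried out can be trusted. The baseline tests address neither. Allocation is random, so a small p-value mostly reflects chance, and at small numbers a large p-value does not show that the arms are alike.

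**Working it through.** **Inputs.** SD 2.5, correlation ρ = 0.5, target difference 1 point, α = 0.05, power 90% and 101 per group (all from Statistical procedures). One-third of 240 is 80 (Discussion). Assumed: two-sided testing, 1:1 allocation (hence 40 per arm), and a baseline SD equal to the planning SD.

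**1. The plan's own figure.** n per group = 2·s²·(1.96 + 1.2816)²/1² = 2·s²·10.507.

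- Change score: s = 2.5·√(2(1 − 0.5)) = 2.5. n = 131.3, so 132 (133 by exact t).
- Conditioned on baseline: s = 2.5·√(1 − 0.5²) = 2.165. n = 98.5, so 99 (100 by exact t).

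At the stated 90% power, 101 agrees closely only with the baseline-conditioned variance. The change score would also give 99–100, but at 80% power, which is not what is stated. Dropout: 101/0.85 = 118.8, consistent with 120.

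**2. Power for 1 point (two-sided t).** The standard error is s·√(2/n).

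| Per arm | Model as listed | Conditioned on baseline |
|---|---|---|
| 40 | SE 0.559, power 42% | SE 0.484, power 53% |
| 101 | SE 0.352, power 81% | SE 0.305, power 90% |

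The ratio of variances is 2.165²/2.5² = 0.75. The listed contrast therefore needs about a third more patients for the same precision (132 against 99).

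**3. Shift given the observed imbalance.** If the baseline means differ by D, the expected change contrast under no effect is ρD − D = −(1 − ρ)D = −0.5·D.

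- The SE of D at 40 per arm is 2.5·√(2/40) = 0.559.
- Median |D| = 0.6745 × 0.559 = 0.377, so the median absolute shift is 0.19 point.
- The largest D with p > 0.05 is 1.991 × 0.559 = 1.11, so the shift is up to 0.56 point.
- At 120 per arm the largest non-significant D is 0.64, with a shift of 0.32.

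Range of the 0.56 figure: 0.22 if ρ = 0.8 (SD 2.5); 0.45 to 0.67 for SD 2 to 3 (ρ = 0.5).

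**4. Error rate.** In 200,000 simulated null trials at 40 per arm, the change contrast rejected in 5.0% overall, and in 4.3% of those with a non-significant baseline SPPB test. At an observed imbalance of exactly 1 point, the conditional rejection rate is about 10%. Power for a true 1-point effect is then about 10% or 79%, depending on which arm started higher.

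**5. What a baseline test can see.** At 40 per arm, a test of baseline SPPB has about 14% power for a true 0.5-point difference and 42% for a 1-point difference.

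**The case against.** **The analysis is valid as it stands.** This is correct. A difference in mean change is a common estimator. It does use baseline, it is unbiased over randomisations, and it holds 5% type I error. A reader might infer from the 10% conditional rate that the primary test is anti-conservative. It is not. That rate belongs to an unusually large imbalance, and over all trials that pass the baseline test the rate is about 4.3%. Likewise, 0.56 point is the edge of the range and 0.19 is typical.

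**The baseline tests do no harm to the estimate.** This is also correct. A reader might infer that comparability will be decided by p-value, or that the tests let a distortion through. The article ties no claim of balance, covariate choice or model choice to them. Its one clause on additional adjustment concerns categorical outcomes and does not mention baseline p-values. The shift in step 3 comes from the model and would be the same if every baseline test were removed.

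**Baseline adjustment may be left to an analysis plan that is not shown.** This does not dispose of the point. The article states the model terms, and those terms do not deliver the stated power at 101 per group.

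**The numbers in hand are provisional.** This stands. The Discussion describes recruitment at the time of writing, and no final number is given. The 40 per arm is an assumption. The loss at 101 per arm does not depend on it.

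**Conclusion.** The point holds as a weakness in efficiency and conditional accuracy, not as bias or inflated error. On the plan's own SD and correlation, the listed model has 81% power at 101 per group where 90% is stated, and about 42% instead of 53% at 40 per arm. In a given trial of 40 per arm, chance imbalance typically moves the SPPB contrast by about 0.19 point. The shift can reach 0.56 point without a significant baseline test. These figures assume two-sided testing, equal allocation and a baseline SD of 2.5. A correlation above 0.5 would reduce the shift. The change is worth making because baseline SPPB is already collected and the recruitment shortfall makes precision scarce. The baseline significance tests are a separate, minor reporting matter: uninformative in randomised groups, but without a stated consequence.

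**What to change.** 1. In Statistical procedures, state that the SPPB contrast at discharge is conditioned on baseline SPPB whatever imbalance is observed. Either enter baseline SPPB as a covariate in a model for the post-baseline values, or keep baseline as an outcome and give both arms a common baseline mean in the mixed model. Either choice matches the variance under which 101 per group gives 90% power.
2. As a minor accompanying change, delete the baseline significance tests and the normality check that selects between them. Keep the means, medians and frequencies by group that are already planned.

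The cost is a few sentences of analysis wording and the loss of a p-value column in the baseline table. No further data or patients are needed. The change should be made before the allocation code is opened.
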